## Methods

### Study design

This is an investigator-initiated, unblinded, multicenter, noninferiority, randomized controlled trial. Randomization has been achieved using a computer-generated randomization sequence, generated by an independent investigator not otherwise involved in the trial, with an allocation ratio of 1:1 and with a permuted block method. A single randomization list was created for all participants. Allocation concealment has been maintained by using sequentially numbered sealed opaque envelopes. Each envelope contains the allocation of the patient to either control (NIV) or intervention (HFNT), with a unique patient identifier code. The randomization is based on a centralized phone call system. Due to the research design, neither the individual collecting data nor the patient can be blinded to treatment allocation.

The study was prospectively registered with ClinicalTrials.gov in December 2017 (identifier: NCT03370666). This protocol has been designed in accordance with the Standardized Protocol Items: Recommendations for Interventional Trials (SPIRIT) guidelines and checklist (Additional file 1). A schedule for enrolment, intervention and assessment (SPIRIT figure) is outlined in Fig. 1. A CONsolidated Standards of Reporting Trials (CONSORT) diagram is shown in Fig. 2.

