### Study endpoints

The primary endpoint of the study will be to evaluate whether HFNT is noninferior to NIV in reducing PaCO_2_, at 2 h after the group allocation, in patients with exacerbation of COPD and mild-to-moderate respiratory acidosis. The secondary endpoints will be: noninferiority of HFNT to NIV in reducing PaCO_2_ at 6 h after randomization; dyspnea score; treatment failure rate; discomfort related to the interface or to symptoms related to airway and mouth dryness; respiratory rate; need for endotracheal intubation; time spent under mechanical ventilation (both invasive and NIV); ICU and hospital length of stay; and hospital mortality.

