### Statistical analysis

For the purpose of the study, we computed a sample size of 56 patients, given an α error of 5% (one-sided) and a β error of 80%, with a standard deviation for the primary outcome equal to 15 mmHg and a noninferiority limit of 10 mmHg [35]. After considering potential drop-outs (30%) [35] and an increase in sample size for nonparametric analysis (15%), the final computed sample size was 80 patients (40 per group).

An independent investigator, blinded to treatment allocation, will undertake all statistical analyses on an intention-to-treat basis. After checking the Gaussian distribution, continuous data will be presented as mean (standard deviation) or median (25th–75th IQR).

Categorical data will be expressed as count and percentage. Continuous data will be compared by the Mann–Whitney *U* test or the Student *t* test, and categorical data by the chi-square test or the Fisher exact test [46]. The Kruskal–Wallis test will be used to check between-group differences at baseline, 2 h and 6 h. Friedman’s test or repeated-measures ANOVA will be used to check within-group differences at different time points. *p* < 0.05 will be considered significant.

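### The primary question is noninferiority at 10 mmHg, but the listed analyses are tests of difference at p < 0.05, with no rule that uses the margin or the one-sided 5% level

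*Protocol article*

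**What the plan says.** The Study design section states: "This is an investigator-initiated, unblinded, multicenter, noninferiority, randomized controlled trial". Under Study endpoints, the primary aim is to "evaluate whether HFNT is noninferior to NIV in reducing PaCO_2_, at 2 h after the group allocation", and the first secondary endpoint puts the same noninferiority question at 6 h.

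The first paragraph of the Statistical analysis section derives 56 patients "given an α error of 5% (one-sided) and a β error of 80" per cent, "with a standard deviation for the primary outcome equal to 15 mmHg" and "a noninferiority limit of 10 mmHg". It then raises the total to 80 for drop-outs and for possible nonparametric analysis.

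The third paragraph of that section turns to testing: "Continuous data will be compared by the Mann–Whitney *U* test or the Student *t* test". It adds chi-square or Fisher tests for categorical data, a Kruskal–Wallis test for differences between arms at baseline, 2 h and 6 h, and Friedman or repeated-measures ANOVA within arms. The only decision threshold is p < 0.05, with no sidedness given. The 10 mmHg limit appears nowhere outside the sample-size statements (Abstract and Statistical analysis).

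**The concern.** A t test, Mann–Whitney test or Kruskal–Wallis test in its ordinary form asks whether the arms differ. The trial asks whether HFNT is worse by less than 10 mmHg. The answers are not interchangeable:

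- A non-significant p-value may only reflect a small sample. It does not exclude a 10 mmHg deficit.
- A significant p-value can arise with an estimated difference below 10 mmHg, so it does not show that HFNT is worse by the margin.
- A Mann–Whitney or Kruskal–Wallis p-value alone gives no estimate in mmHg to set against the limit. The plan expects it may need this route, because it enlarges the sample for nonparametric analysis.

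Followed as written, the plan leaves the primary conclusion either without a rule or resting on the absence of significance. The Discussion says that a noninferior result would allow physicians to use HFNT as an alternative to NIV, so how noninferiority is declared matters in practice.

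**Working it through.** **Inputs.** From Statistical analysis: SD 15 mmHg, limit 10 mmHg, one-sided 5%, 56 patients before inflation and 80 after. From Study design: 1:1 allocation. Assumed, because not stated: true difference 0 for power. The 80 per cent described as β error is taken as power, since that reproduces the stated 56.

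**1. Reproducing the plan's own figure.**

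n per arm = 2 × (z₀.₉₅ + z₀.₈₀)² × SD² / margin² = 2 × (1.645 + 0.842)² × 225/100 = 27.8, so 28 per arm and 56 in total. This matches. At one-sided 2.5% the same formula gives 2 × (1.960 + 0.842)² × 2.25 = 35.3, so 36 per arm and 72 in total, which does not match. The 56 therefore rests on a test against the 10 mmHg margin at one-sided 5%.

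**2. Standard errors.** SE = 15 × √(2/n): 4.01 mmHg at 28 per arm and 3.35 mmHg at 40 per arm. These two sizes span the range from the 56 before inflation to all 80 patients evaluable.

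**3. What happens if a non-significant difference is read as noninferiority.** Put the true difference exactly at the margin, 10 mmHg. The t statistic is then noncentral t with 2n − 2 degrees of freedom and noncentrality 10/SE (2.49 and 2.98). The chance of a non-significant result is:

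| Rule | 28 per arm | 40 per arm |
|---|---|---|
| Two-sided p > 0.05 | 31.2% | 16.2% |
| One-sided p > 0.05 (testing HFNT worse) | 20.7% | 9.5% |
| Margin test at the planned level | 5% | 5% |

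The article does not give the sidedness of p < 0.05, so both readings are shown. Both exceed 5%.

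**4. Where the two rules disagree.** With an observed SD of 15, the two-sided test is non-significant while the observed HFNT excess is below t₀.₉₇₅ × SE. Noninferiority at one-sided 5% needs an excess below 10 − t₀.₉₅ × SE.

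| | 28 per arm | 40 per arm |
|---|---|---|
| Half-width of 95% CI (limit of non-significance) | 8.0 mmHg | 6.7 mmHg |
| Half-width of 90% CI | 6.7 mmHg | 5.6 mmHg |
| Largest excess that meets noninferiority | 10 − 6.7 = 3.3 mmHg | 10 − 5.6 = 4.4 mmHg |

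An observed excess between 3.3 and 8.0 mmHg (28 per arm), or between 4.4 and 6.7 mmHg (40 per arm), is not significant under the written threshold yet fails noninferiority.

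**5. Effect of the level on power.** Power = Φ(10/SE − z).

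| Interval set against 10 mmHg | 28 per arm | 40 per arm |
|---|---|---|
| 90% CI (one-sided 5%, as sized) | Φ(2.494 − 1.645) = 80.2% | Φ(2.981 − 1.645) = 90.9% |
| 95% CI (one-sided 2.5%) | Φ(2.494 − 1.960) = 70.3% | Φ(2.981 − 1.960) = 84.6% |

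The t-based value for the 95% CI at 28 per arm is 68.8%. If p < 0.05 is taken as two-sided and carried over to a 95% interval, the 56 no longer gives 80% power.

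**The case against.** A journal article condenses the full plan, and the mechanics of a noninferiority test could sit in an analysis plan that is not shown. The article does state the margin, the one-sided level, the endpoint and the time point. The sentence on continuous data is generic and does not single out the primary endpoint. Nowhere does the article say that a non-significant result will be read as noninferiority. Both named procedures can be run against a null shifted by 10 mmHg, and inverting the Mann–Whitney test gives a shift estimate in mmHg. On that view only a linking sentence is missing, and the 31% and 16% describe a misuse that the article does not prescribe.

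Part of this stands. The margin and the one-sided level are used, but only for the sample size. The error rates are conditional on reading non-significance as noninferiority, and the 70% power figure on choosing a 95% interval and having 56 evaluable patients. The named families of tests need not be abandoned.

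The main point is not met. The article does not defer the matter: it lists its tests and a threshold. The one test tied explicitly to 2 h and 6 h is the Kruskal–Wallis test, which is described as checking for differences and has no direction. No shifted null, confidence interval or link to the one-sided 5% is given. An unseen analysis plan could repair this, but the published text would still contradict its own primary endpoint.

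**Conclusion.** The concern holds. The design, the primary endpoint and the sample size all rest on a noninferiority comparison at 10 mmHg and one-sided 5%, while the stated analysis consists of difference tests at p < 0.05. Followed as written, that analysis cannot establish noninferiority at 2 h or 6 h.

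If non-significance on a two-sided t test were taken as noninferiority, the false-claim rate at the margin would be about 31% at 28 per arm and 16% at 40 per arm, assuming normal data and SD 15. The mismatch itself does not depend on those assumptions. The design can support a proper margin test once one is stated. This must be fixed before the data are analysed.

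**What to change.** State a decision rule for PaCO₂ at 2 h, and the same rule at 6 h:

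- Estimate the HFNT minus NIV difference in mmHg, saying whether it refers to the PaCO₂ level or to the change from baseline. The rule works for either.
- Declare noninferiority if the upper limit of the one-sided 95% confidence interval (equivalently, of the two-sided 90% interval) is below 10 mmHg.
- If the data are clearly non-normal, set a Hodges–Lehmann shift interval or a bootstrap interval against the same 10 mmHg. Specify in advance which one.
- Keep p < 0.05, with its sidedness stated, for difference tests on the other secondary endpoints, and say that a non-significant test is not evidence of noninferiority.

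This matches the stated level and margin, so the 56 patients before inflation are unchanged. If a two-sided 95% interval is preferred, the figure before inflation becomes 72. The cost is two or three sentences in the protocol or analysis plan before database lock, with no extra patients or data under the 90% interval.

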### Data collection and outcome assessment

For each patient, we will collect anthropometric data (age, gender, weight and height) and baseline characteristics (the Simplified Acute Physiology Score (SAPS II), the Kelly-Matthay score [36], the Charlson index [37] and the Richmond Agitation Sedation Scale (RASS) score [38]). Furthermore, soon before randomization we will record vital parameters (heart rate, blood pressure, breath frequency and temperature), the amount of secretions, the presence of dyspnea (as reported by the patient through the Borg scale) [39] and arterial blood gases (ABGs) at patient inclusion.

At 2 and 6 h after the patient’s randomization to receive NIV or HFNT, we will collect all vital parameters, ABGs, the RASS score, the Kelly-Matthay score [36], the grade of dyspnea and the need for sedatives. Sedation will be allowed to increase tolerance to the treatment [40, 41]. Moreover, we will record: the settings of NIV and HFNT; the discomfort related to the interface, as assessed through a 11-point Numeric Rating Scale (NRS) [15, 42, 43]; and the intolerance to the interface due to flow, temperature, noise, claustrophobia, sweating, tightness, airway dryness, vomiting gastric distension, ocular irritation or skin breakdown, separately [42, 44, 45].

We will also record: the rate of treatment intolerance, as defined by the inability of the patient in continuing NIV or HFNT treatment; the rate of treatment failure, as defined by the presence of PaCO_2_ worsening or reduction < 10 mmHg from baseline assessment, or worsening or no improvement of dyspnea, or respiratory rate > 30 breaths/min; need for endotracheal intubation; time spent under mechanical ventilation (both invasive and NIV); ICU and hospital length of stay; and hospital mortality.

The decision to intubate the patient will be taken by the physician in charge of the patient, in the case of the presence of one of the following criteria: respiratory arrest, respiratory apnea or pauses with loss of consciousness, severe agitation, bradycardia (< 50 beats/min) with loss of consciousness, hemodynamic instability with systolic arterial pressure < 70 mmHg, need for invasive mechanical ventilation due to worsening in arterial blood gases and pH, need for suctioning due to unmanageable secretions or intolerance to all of the interfaces (including shift of treatment to NIV in the HFNT group).

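### Arms are compared only by unadjusted tests although every patient has a baseline PaCO2; a single baseline-adjusted primary analysis would be more precise at almost no cost

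*Protocol article*

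**What the plan says.** All references are to the protocol article; no separate analysis plan was available.

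- **Study endpoints.** The primary endpoint is noninferiority of HFNT to NIV in reducing PaCO2 2 h after allocation, and the 6 h comparison is secondary. The section does not say whether the variable is the 2 h value or the change from baseline.
- **Data collection and outcome assessment.** Shortly before randomization the investigators record "arterial blood gases (ABGs) at patient inclusion", and blood gases are repeated at 2 h and 6 h.
- **Statistical analysis, between arms.** Continuous data are compared by Mann–Whitney or Student t. In addition, "The Kruskal–Wallis test will be used to check between-group differences at baseline, 2 h and 6 h".
- **Statistical analysis, within arms.** Friedman's test or "repeated-measures ANOVA will be used to check within-group differences at different time points".
- **Statistical analysis, sample size.** The calculation uses a one-sided 5% alpha, "with a standard deviation for the primary outcome equal to 15 mmHg" and "a noninferiority limit of 10 mmHg", and reports that "we computed a sample size of 56 patients", raised to 80 (40 per group).

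**The concern.** The outcome is a physiological measurement taken on the same patient before and after treatment starts, so the baseline value is usually its best single predictor. The article names its between-arm tests, and none of them conditions on that value. In a trial of 80 patients, chance differences in baseline PaCO2 can be sizeable against a 10 mmHg margin. The Study design section describes one list with permuted blocks and mentions no stratification on PaCO2 that would limit them.

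Two of the listed tests also add nothing to the primary question. Kruskal–Wallis with two groups repeats Mann–Whitney. Testing the arms against each other at baseline asks whether randomization produced a chance difference, which is already known to be the only possible source if allocation was sound.

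At stake is precision: how wide the interval for the PaCO2 difference will be, and so how likely a truly noninferior treatment is to be shown noninferior.

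**Working it through.** **1. The plan's own figure.** Inputs from Statistical analysis: one-sided alpha 0.05, SD 15, margin 10. Two inputs are inferred. The true difference is taken as 0 because that reproduces the result. Power is taken as 80%: the article prints this figure as the β error, but read literally that would need only about 3 per arm.

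n per arm = 2 × [15 × (1.645 + 0.842) / 10]² = 27.8, so 28 per arm and 56 in total. The stated size is reproduced exactly, without adjustment.

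Power = Φ(10 / (SD × √(2/n)) − 1.645):
- n = 28: 10 / 4.01 − 1.645 = 0.85, power 80.2%.
- n = 40: 10 / 3.35 − 1.645 = 1.34, power 90.9%.

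These two sizes bracket the trial: 40 per arm is full data, and 40 × 0.70 = 28 is what remains after the allowed 30% drop-out.

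**2. Effect of adjusting for baseline.** Let r be the correlation between baseline and 2 h PaCO2, with equal SDs at both times. Both are assumptions; the documents give neither. The residual SD under ANCOVA depends on what the 15 mmHg describes:
- (A) SD of the 2 h value: 15 × √(1 − r²).
- (B) SD of the change: 15 × √((1 + r)/2).

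Example (A), r = 0.5: 15 × √0.75 = 12.99; 10 / (12.99 × √(2/28)) − 1.645 = 1.24; power 89%.

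| r | A: SD | A: N for 80% | A: power at 28 / 40 per arm | B: SD | B: N for 80% | B: power at 28 / 40 per arm |
|---|---|---|---|---|---|---|
| 0.3 | 14.31 | 52 | 83% / 93% | 12.09 | 38 | 93% / 98% |
| 0.5 | 12.99 | 42 | 89% / 96% | 12.99 | 42 | 89% / 96% |
| 0.6 | 12.00 | 36 | 93% / 98% | 13.42 | 46 | 87% / 95% |
| 0.7 | 10.71 | 30 | 97% / 99% | 13.83 | 48 | 86% / 94% |
| 0.8 | 9.00 | 22 | 99% / >99% | 14.23 | 52 | 84% / 93% |

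The unadjusted reference is N = 56 and 80% / 91% throughout. The gain grows with r under (A) and shrinks with r under (B), but adjustment helps under both.

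**3. A change score is not a substitute.** Under (A) the SD of the change is 15 × √(2(1 − r)), which is 17.75, 15.00 and 11.62 at r = 0.3, 0.5 and 0.7. The required N is then 78, 56 and 34. The change beats the raw 2 h value only if r exceeds 0.5, and at each of these r it needs more patients than ANCOVA (52, 42 and 30).

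**4. Chance imbalance.** If the baseline SD is also 15 (an assumption), the standard error of the baseline difference is 15 × √(2/40) = 3.35 mmHg, so the 95% range is ±1.96 × 3.35 = ±6.6. At 28 per arm it is ±1.96 × 4.01 = ±7.9. With equal SDs, r times the imbalance carries into the 2 h difference. At 40 per arm, 6.6 × 0.3 = 2.0, 6.6 × 0.5 = 3.3 and 6.6 × 0.7 = 4.6 mmHg, against a margin of 10.

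**5. Cost if baseline predicts nothing (r = 0).** With t-based power at 28 per arm, one fewer degree of freedom and the SD multiplied by √(1 + 1/52), power falls from 79.3% to 78.6%, about 0.7 points.

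**6. Kruskal–Wallis.** With two groups it is the Mann–Whitney test. In one simulated data set both gave p = 0.0318 (asymptotic, no continuity correction).

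**The case against.** The strongest reply is that an unadjusted comparison is valid under randomization and the design meets its power target with it. That stands. A reader might infer from this point that power has been lost. It has not: the 56 is an unadjusted figure, and adjustment adds to it.

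A reader might also infer that the baseline is ignored altogether. The documents do not establish that. Reducing PaCO2 may mean a change from baseline, and the treatment-failure definition does speak of a reduction from baseline; a t or Mann–Whitney test could be applied to such a change. Against this, the Kruskal–Wallis sentence includes the baseline time point, where no change exists, so that sentence at least compares levels. What can be said is that the variable is undefined and no adjusted comparison is named.

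Nor does a baseline imbalance pass in full into the 2 h result. Only about r times it does, and that variation is already in the unadjusted standard error. The limits on PaCO2 and pH at entry may narrow the baseline spread and lower r.

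The within-arm tests are not presented as evidence between arms. Regression to the mean and background therapy affect changes within an arm but should not bias a randomized comparison, so these tests can remain as description.

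Finally, covariate adjustment may appear in a plan not seen here. But the article is not silent on the matter: it names its between-arm tests, and this point concerns those.

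**Conclusion.** The point holds as an efficiency improvement that should be made, not as a repair of an invalid analysis. The stated between-arm tests leave unused a baseline value collected in every patient, one of them is redundant, and the primary variable is not fixed.

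The size of the gain is uncertain because the documents give neither r nor the meaning of the 15 mmHg. Over the r values tabulated, power at 28 per arm rises from 80% to between 83% and 99%. At 40 per arm the room for gain is smaller, from about 91% to between 93% and over 99%. The direction does not depend on which SD reading is right, provided r is not close to zero under reading (A). Adjustment accounts for chance imbalance in baseline PaCO2 only, not in other prognostic factors.

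**What to change.** - State the primary variable, and say whether 15 mmHg is the SD of the 2 h value or of the change.
- Make the primary analysis a single ANCOVA: PaCO2 at 2 h on arm and baseline PaCO2. Report the adjusted HFNT minus NIV difference with a two-sided 90% confidence interval, which matches the one-sided 5% alpha. Conclude noninferiority only if its upper limit is below 10 mmHg. Without that comparison with the margin, adjustment does not answer the primary question.
- Keep a rank-based or robust version as a sensitivity analysis, since the article anticipates non-Gaussian data.
- Analyse 6 h in the same way.
- Drop the Kruskal–Wallis test and the significance tests at baseline; describe baseline by arm instead.

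The cost is one degree of freedom (about 0.7 points of power if r = 0) and the usual linear-model assumptions. The change is one of wording, to be made before the data are analysed.

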### Study organization

The steering committee consists of two principal investigators (AC, FL) plus six members with recognized expertise on NIV/HFNT in COPD patients. The steering committee invited other centers based on expertise and availability of study patients and materials. Each participating center has a local principal investigator in charge. They act as the guarantors of the data, and are responsible for data management and storage in their centers. Local principal investigators also communicate with the principal investigators and transfer patient data in an anonymized form on standard case report forms; in the case of logistic difficulties or study doubts, the local investigators can ask for immediate phone call support from principal investigators, to achieve adequate participant enrolment. Data monitoring will be done by an ndependent investigator serving as the data manager. This will be done by means of queries on the final databases, after collecting the case report forms from enrolling centers, to check for abnormalities and inconsistencies.

## Discussion

HFNT is increasingly used in different settings [23, 25–27]. Some studies indicate that HFNT has physiological advantages in both stable and exacerbated COPD patients [20]; in particular, in patients recovering from an episode of hypercapnic ARF due to COPD exacerbation, HFNT reduces the respiratory effort and rate no differently from NIV, while it maintains similar gas exchanges and improved comfort [22]. A recent observational trial found no difference between NIV and HNFT in terms of 30-day mortality and intubation rate in severe exacerbation of COPD [34].

Currently, NIV is strongly suggested as standard treatment for exacerbated COPD patients with respiratory acidosis [3]. However, NIV is affected by several drawbacks such as reduced comfort and poor patient–ventilator interaction and synchrony, which is often difficult to be recognized and managed [4, 11–13, 16]. We therefore design this randomized controlled trial to assess the noninferiority of HFNT in reducing the PaCO_2_, as compared to NIV. In fact, whenever the trial demonstrates a noninferiority of HFNT compared to NIV, the physician may use HFNT as an alternative ventilatory support in exacerbated COPD patients with mild-to-moderate respiratory acidosis. This would also allow the possibility to use another support with a different interface in a rotational strategy to improve the patient’s comfort and tolerance to the treatment [47, 48]. This trial has limitations. First, blinding is not possible due to the nature of the interventions. Second, although recruitment centers have established experience in the use of ventilator support in this patient population, different practices in the use of both NIV and HNFT may influence the effect of the interventions. However, recruitment centers have established experience in the use of ventilator support in this patient population. Third, the study is a noninferiority trial with a physiologic outcome, leaving uncertainty on stronger patient-related outcomes. It is anticipated that the results of this study will be used to design further randomized clinical trials powered to assess major clinical outcomes.

